5.1.1　Primary endpoint

Achievement of at least 20% reduction in volume of venous malformations from baseline (prior to administration) at 3 months of treatment with the investigational drug

[Basis for setting up].

Validity of the evaluation items:

In an ongoing Japanese investigator-initiated clinical trial of oral sirolimus treatment for lymphatic malformations, which is a similar disease of venous malformations, a 20% or greater reduction in the volume of the target lesion on MRI is considered a partial response (PR). Since the presence of a lesion can cause various symptoms, a reduction in volume of 20% or more is clinically significant. In addition, many literature studies have shown that patients with lesion reduction also experience improvement in pain.

In a trial conducted in the U.S. for oral sirolimus treatment of refractory vascular malformations, one of the endpoints was a 20% or greater reduction in the volume of the target lesion by MRI as PR, and the above domestic trial is based on this evaluation standard.

Validity of the evaluation period:

In evaluating the efficacy of sclerotherapy with monoethanolamine oleate, previous reports include Kaji et al.^5)^ evaluated by MRI at 3 months after treatment; Hoque et al.^6)^ evaluated at 8 weeks after sclerotherapy. A trial of gastric varices with a similar mechanism evaluated at 90 days after treatment. Based on these previous reports, the evaluation period was set at 3 months.

Regarding safety, Nomura et al. reported^9)^ that skin necrosis or mucous membrane necrosis was observed in 14.7% of patients, but all of them improved with conservative treatment. The average time required for healing was 58.6 days (maximum approximately 90 days). Generally, the adverse drug reactions by sclerotherapy occur within a few days of treatment, and considering the period until the adverse drug reactions are cured as the necessary observation period, it is reasonable to set the evaluation period at 3 months.

5.1.2　Secondary endpoint(s)

5.1.2.1　Significant secondary endpoint

Improvement from baseline (prior to administration) in symptoms (pain) associated with the target lesion after 3 months of sclerotherapy*.

*: For pain rating scales, VAS is used for patients aged 6 years and older. Face scale is used for patients aged 2 to 5 years of age, however, evaluation for this group is not mandatory. For guardians, VAS is used if the patient is 6 to 14 years old, and Face scale is used if the patient is 5 years old or younger, and the evaluation should be done from the guardian’s perspective.. (The evaluation scale is shown in Appendix 2.)

For patients

| Patient Age | | 0 year old | 1 year old | 2-4 years old | 5 years old | 6-7 years old | 8-12 years old | 13-14 years old | 15 years and older |
| --- | --- | --- | --- | --- | --- | --- | --- | --- | --- |
| Pain | VAS |  |  |  |  | X | X | X | X |
|  | Face scale |  |  | X** | X** |  |  |  |  |

**: Evaluation is not mandatory.

For guardians

| Patient Age | | 0 year old | 1 year old | 2-4 years old | 5 years old | 6-7 years old | 8-12 years old | 13-14 years old | 15 years and older |
| --- | --- | --- | --- | --- | --- | --- | --- | --- | --- |
| Pain | VAS |  |  |  |  | X | X | X |  |
|  | Face scale | X | X | X | X |  |  |  |  |

[Basis for setting up].

In diffuse lesions, we considered it particularly important to see improvement in pain, therefore we set this as a significant secondary endpoint.

5.1.2.2　Other secondary endpoints

The efficacy endpoints are as follows:

1) Reduction rate in volume of venous malformations at the time of 3 months after intervention

2) Improvement in symptoms such as pain originated from venous malformations at the time of 1 month (4 weeks) after intervention^＊^

3) Improvement of QOL (ADL) at the time of 3 months after intervention^＊＊^

*: For pain rating scales, VAS is used for patients aged 6 years and older; Face scale is used for patients aged 2 to 5 years, however, evaluation for this group is not mandatory. For guardians, VAS is used if the patient is 6 to 14 years old, and Face scale is used if the patient is 5 years old or younger to evaluate from the guardian’s perspective. (The evaluation scale is shown in Appendix 2.)

**: For the QOL evaluation scales, the EQ-5D Japanese version is used for patients aged 15 years and older, and the PedsQL Japanese version for patients aged 5 to 14 years, however, evaluation for children aged 5 years is not mandatory. For guardians, the PedsQL Japanese version (proxy evaluation) is used if the patient is 14 years old or younger, and the evaluation should be done from the guardian’s perspective. The selection of the QOL evaluation scale was determined based on the review of the QOL Evaluation Method Review Committee. (The evaluation scale is shown in Appendix 2.)

For patients

| Patient Age | | 0 year old | 1 year old | 2-4 years old | 5 years old | 6-7 years old | 8-12 years old | 13-14 years old | 15 years and older |
| --- | --- | --- | --- | --- | --- | --- | --- | --- | --- |
| Pain | VAS |  |  |  |  | X | X | X | X |
|  | Face scale |  |  | X***. | X***. |  |  |  |  |
| QOL | EQ-5D |  |  |  |  |  |  |  | X |
|  | PedsQL |  |  |  | X***. | X | X | X |  |

****: Evaluation is not mandatory.

For guardians

| Patient Age | | 0 year old | 1 year old | 2-4 years old | 5 years old | 6-7 years old | 8-12 years old | 13-14 years old | 15 years and older |
| --- | --- | --- | --- | --- | --- | --- | --- | --- | --- |
| Pain | VAS |  |  |  |  | X | X | X |  |
|  | Face scale | X | X | X | X |  |  |  |  |
| QOL | PedsQL | X | X | X | X | X | X | X |  |

5.1.3　Other endpoint

Change in appearance at the time of 3 months after intervention; significant improvement, moderate improvement, no change and exacerbation.

5.2　Safety endpoints

1. Adverse events and Adverse drug reactions
2. Clinical laboratory test

5.2.1　Adverse event assessment

5.2.1.1　Definition of adverse events

Adverse event

An adverse event is defined as any unfavorable medical events that occur to patients from the time of informed consent is obtained until the end of the observation period (up to 3 months after the administration of the investigational drug, or up to 3 months after the administration of an additional dose in the case of additional treatment), regardless of whether or not it is causally related to the treatment.

Serious adverse events

Serious adverse events (SAEs) are defined as follows:

- Leading to death
- Life-threatening
- Requiring hospitalization or extended hospitalization for treatment
- Permanent or marked disability or dysfunction
- Resulting in congenital anomalies
- Adverse events that are considered serious for other reasons include medically significant events that, based on appropriate medical judgment, may endanger the subject or require medical or surgical procedures that do not meet the definition above.

The term "life-threatening" in this definition means that the subject was at risk of death when the event occurred, not in the hypothetical sense that death might have resulted had the event been more severe.

Newly developed cancer must be reported as a serious adverse event regardless of the time between discontinuation of the investigational drug and the development of the cancer.

Adverse events that may lead to disability are reported as serious adverse events as other medically significant conditions.

Notable Significant Adverse Events

The following events are defined as significant adverse events of interest for the safety profile.

Skin necrosis occurring after administration

Visual impairment occurring after administration (in case of facial lesions)

If a significant adverse event occurs, the investigator or subinvestigator shall promptly inform the Coordinating Committee via E-mail. The clinical trial shall be conducted with caution, referring to "4.1.12 Criteria for discontinuation of investigational drug" and "4.2.2 Emergency medications, emergency procedures, additional concomitant medications/adjunctive therapies"

Severity of adverse events

The severity of the adverse event is determined by the following criteria and recorded in the CRF

Mild: easily tolerated signs or symptoms

Moderate: Signs or symptoms that interfere with daily life

Severe: Signs or symptoms of severe impairment to the extent that daily life is no longer possible.

Causal relationship with investigational drug

The causal relationship between the investigational drug and the adverse event shall be determined and recorded in the CRF using the following criteria, taking into consideration all relevant factors including the pattern of occurrence of the adverse event, temporal relationship, circumstances when the investigational drug was discontinued or re-administered, and confounding factors such as concomitant therapy, complications, and history of the event.

Causal relationship exists: a reasonable causal relationship exists between the administered investigational drug and the adverse event.

No causal relationship: other than above

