5.2.1.2　Collection and reporting of adverse events

Collection of adverse events

The investigator and subinvestigator will collect and record the following adverse events on the CRF

- From the time of informed consent is obtained until the end of the observation period for each subject (up to 3 months after the administration of the study drug. In the case of additional treatment, until 3 months after the additional administration):

All adverse events (serious and non-serious)

- After the completion of the clinical trial for the individual subject:

When investigators and subinvestigators become aware of serious adverse events (SAEs) that cannot be denied as causally related to the investigational drug, they must promptly report such events. The period for collecting information shall be until the completion of this entire clinical trial (until the last observation date of the last subject).

Reporting of adverse events to the head of the site, the Coordinating Committee, and the investigational drug provider, and the procedures for reporting adverse events

1. When an SAE occurs, the investigator and subinvestigator must immediately report it to the head of the site and to the Coordinating Committee using the unified forms "Form 12 (Report on Serious Adverse Events)" and "Form for Detailed Description".
2. The Coordinating Committee shall review the content of the SAE obtained from the investigator or subinvestigator and notify the investigators at other sites of the information regarding the SAE.
3. The investigator at each site shall review the content of the SAE information obtained from the Coordinating Committee, discuss it with the Coordinating Committee as necessary, and report his/her opinion as an investigator (including the necessity of reporting to the Ministry of Health, Labour and Wealth (MHLW)) to the Coordinating Committee.
4. The Coordinating Committee shall report promptly to the investigational drug provider by e-mail using the same form as in (1).
5. When additional information on these events is obtained, a SAE reporting form should be submitted as an additional report. The same rules and procedures will be followed for any additional information.

Reporting of adverse events to the MHLW and its procedures

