The Coordinating Committee must report to the MHLW within the established time limit if the case falls under a reportable case (SAE for which a causal relationship with the investigational drug cannot be denied) as stipulated in Article 273 of the Enforcement Regulations of the Pharmaceutical Affairs Law.

Required Information

For each adverse event, the investigator and subinvestigator shall record the necessary information (onset date, disappearance date, severity, treatment, outcome, severity, treatment with the investigational drug, etc.) in the CRF. In addition, investigators and subinvestigators must determine the causal relationship between all adverse events and the investigational drug.

The following events will also be treated as adverse events

・Aggravation of primary or pre-existing disease

・Fluctuations in vital signs, electrocardiograms, physical findings, and laboratory values that the investigator and subinvestigators consider clinically problematic

If such abnormalities existed prior to inclusion in the clinical trial, they are considered the baseline condition of the subject.

All adverse events, including those that persist at the end of a clinical trial for an individual subject, should be followed to the extent possible until the subject recovers to the state prior to the adverse event, or until the event is fully investigated or no new information is available.

6.　Investigational plan

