8.2.3　Safety analysis

(1) For each adverse event and adverse drug reaction, the number of subjects and incidence rate are shown. The number of subjects and the incidence rate is tabulated by organ, symptoms findings, and grade of adverse event. For serious adverse events, the number of subjects and the rate of occurrence should is indicated and listed.

(2) Summary statistics of laboratory measurements are tabulated by survey period.

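### The CRF causality code and the reporting rules in the protocol use different standards, so events of doubtful cause may be left out of the adverse drug reaction table

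*Protocol*

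**What the plan says.** Protocol 5.2 names adverse events and adverse drug reactions together as the first safety endpoint. Section 8.2.3 tabulates both: "For each adverse event and adverse drug reaction, the number of subjects and incidence rate are shown".

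Section 5.2.1.1, under the causal relationship paragraph, says that causality "shall be determined and recorded in the CRF using the following criteria". There are two levels:

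- Related: "Causal relationship exists: a reasonable causal relationship exists between the administered investigational drug and the adverse event".
- Unrelated: "No causal relationship: other than above".

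There is no level for possible, unknown or not excluded. Under Required Information, 5.2.1.2 asks for a causality judgement on every adverse event, so this code is completed for all of them.

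Elsewhere, 5.2.1.2 uses a different standard in two places. After a subject has completed, investigators report "serious adverse events (SAEs) that cannot be denied as causally related to the investigational drug". For reports to the ministry, the reportable case is an "SAE for which a causal relationship with the investigational drug cannot be denied".

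While a subject is under observation, reporting within the trial has no causality condition: "When an SAE occurs, the investigator and subinvestigator must immediately report it to the head of the site and to the Coordinating Committee".

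**The concern.** The two standards put the burden in opposite places. The CRF code needs a positive finding, and anything short of it becomes unrelated. The reporting standard needs a link to be ruled out, and anything short of that counts as drug-related. An event in between is treated in opposite ways.

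Such events are plausible in this trial. Treatment involves contrast medium (4.1.4, 4.1.8), general or local anaesthesia (4.1.8), compression and, where needed, steroids (4.1.8, 4.1.9). Section 5.2.1.1 itself tells the assessor to weigh concomitant therapy as a confounder. With no control arm, attribution rests on the individual judgement and on how the form lets it be recorded.

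Two things are at stake. The adverse drug reaction incidence may be understated and may disagree with the trial's own ministry reports. Sites may also code the same doubtful event differently, because the form does not say where it belongs.

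**Working it through.** The protocol states no figure that depends on the causality rule, so there is none to reproduce. The check compares the texts and then scales the possible effect.

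**Step 1: how each rule treats an event**

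| Event | CRF code (5.2.1.1) | Reporting standard (5.2.1.2), if serious |
| --- | --- | --- |
| Reasonable causal relationship found | related | drug-related |
| Link doubtful but not excludable | unrelated, as the residual class | drug-related |
| Link can be denied | unrelated | not drug-related |

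The rules disagree only in the middle row. No section says how one standard maps to the other.

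**Step 2: where the mismatch can reach the results**

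- Adverse event tables: unaffected. Section 5.2.1.1 defines adverse events without regard to cause, and 5.2.1.2 collects all of them to the end of observation.
- Serious event count and list in 8.2.3: unaffected, since neither depends on causality.
- Adverse drug reaction table in 8.2.3: affected if it is built from the CRF code. The protocol does not define an adverse drug reaction or name the source of this table. The CRF code is the only relatedness item it specifies for every event, so its use here is an inference, though the natural one.
- Serious events found after a subject completes: these lie outside the adverse event window in 5.2.1.1. The disagreement that can reach the table therefore concerns events within the window.

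**Step 3: what a later analysis plan could recover**

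For serious events, the ministry reports and the investigators' opinions on whether to report offer a second source. For non-serious events no second source is specified: a doubtful event and a clearly unrelated one carry the same code, and the distinction is lost when the form is completed.

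**Step 4: scale**

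Inputs: 22 subjects per cohort and 44 in all (8.6.1). The number k of subjects whose doubtful event is coded unrelated is not given, so k is an assumption. The change in the incidence of a given reaction is k/n.

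| k (assumed) | Cohort of 22 | All 44 |
| --- | --- | --- |
| 0 | 0 | 0 |
| 1 | 1/22 = 4.5 points | 1/44 = 2.3 points |
| 2 | 2/22 = 9.1 points | 2/44 = 4.5 points |
| 3 | 3/22 = 13.6 points | 3/44 = 6.8 points |

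For a reaction seen in one subject of a cohort, recoding that subject turns 1/22 (exact 95% interval 0.1% to 22.8%) into 0/22 (97.5% upper limit 15.4%). The change in adverse event incidence is 0 in every row.

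**The case against.** The strongest reply is that the standards serve different purposes. The ministry criterion restates a legal trigger for a duty of the Coordinating Committee, and a cautious trigger can sit beside a clinical judgement on the CRF without error. That is fair as to purpose. It does not tell an investigator how to code an event that meets the trigger but not the CRF definition, nor which standard defines the tabulated reaction.

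A second reply is that a reasonable causal relationship need not mean a proven one. An investigator could read it to include plausible but unproven cases, and the two standards would then nearly coincide. This stands in part: a broad reading narrows the gap. It leaves the rule ambiguous, however, because the residual class is labelled as no relationship and sites may read the positive class differently.

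A third is that some obvious examples would probably be coded as related anyway. Section 2.3 already lists haemoglobinuria and renal deterioration as things to look for after dosing, and 6.2.3.3 speaks of abnormal renal function associated with administration. That also stands, so the case does not rest on any one example.

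Finally, the size is assumed. Zero affected subjects is possible, and the shift applies per reaction term. Section 2.3 cites a study with local tenderness and swelling in all patients, so the incidence of any reaction may be near its ceiling whatever the coding. All of this is accepted.

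**Conclusion.** The point holds as an inconsistency within 5.2.1. Read literally, one serious event can be reported to the ministry as drug-related and coded unrelated in the CRF. If 8.2.3 draws on that code, each affected subject lowers the incidence of a given reaction by 4.5 points in a cohort of 22, or by 2.3 points of all 44. This rests on two assumptions: that the reaction table uses the CRF code, and that some events fall between the two standards. Their number is unknown.

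A reader might infer more than the document supports:

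- That doubtful events vanish from the safety endpoint. They stay in the adverse event tables and, if serious, in the serious event list; only the reaction table can lose them.
- That all urgent reporting uses the wider standard. Within the trial every serious event is reported without a causality condition; the wider standard covers only ministry reports and serious events found after completion.
- That a downward bias is shown, or that the reaction table is the main safety result. The first is a possibility of unknown size. On the second, 8.2.3 gives adverse events and reactions equal standing, and 5.2.1.1 describes the events of special interest by their occurrence after administration, not by cause.
- That no analysis plan could repair it. For serious events other records may preserve the information; the loss is firm only for non-serious ones.

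This is a cheap improvement worth making.

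**What to change.** Reconcile 5.2.1.1 and 5.2.1.2 to one criterion. For example, define the positive code as a reasonable possibility of a causal relationship, meaning that it cannot be denied, and the negative code as a causal relationship that can be denied. Then state that the positive code defines an adverse drug reaction for 8.2.3. The CRF, the reaction table and the ministry reports would then use one standard.

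The cost is one definition in the protocol and a matching line in the CRF instructions. The downside is that the reported adverse drug reaction incidence may be slightly higher. Adverse event incidence, treatment and the assessment schedule are unaffected.

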5.2.1.2　Collection and reporting of adverse events

Collection of adverse events

The investigator and subinvestigator will collect and record the following adverse events on the CRF

- From the time of informed consent is obtained until the end of the observation period for each subject (up to 3 months after the administration of the study drug. In the case of additional treatment, until 3 months after the additional administration):

All adverse events (serious and non-serious)

- After the completion of the clinical trial for the individual subject:

When investigators and subinvestigators become aware of serious adverse events (SAEs) that cannot be denied as causally related to the investigational drug, they must promptly report such events. The period for collecting information shall be until the completion of this entire clinical trial (until the last observation date of the last subject).

Reporting of adverse events to the head of the site, the Coordinating Committee, and the investigational drug provider, and the procedures for reporting adverse events

1. When an SAE occurs, the investigator and subinvestigator must immediately report it to the head of the site and to the Coordinating Committee using the unified forms "Form 12 (Report on Serious Adverse Events)" and "Form for Detailed Description".
2. The Coordinating Committee shall review the content of the SAE obtained from the investigator or subinvestigator and notify the investigators at other sites of the information regarding the SAE.
3. The investigator at each site shall review the content of the SAE information obtained from the Coordinating Committee, discuss it with the Coordinating Committee as necessary, and report his/her opinion as an investigator (including the necessity of reporting to the Ministry of Health, Labour and Wealth (MHLW)) to the Coordinating Committee.
4. The Coordinating Committee shall report promptly to the investigational drug provider by e-mail using the same form as in (1).
5. When additional information on these events is obtained, a SAE reporting form should be submitted as an additional report. The same rules and procedures will be followed for any additional information.

Reporting of adverse events to the MHLW and its procedures

The Coordinating Committee must report to the MHLW within the established time limit if the case falls under a reportable case (SAE for which a causal relationship with the investigational drug cannot be denied) as stipulated in Article 273 of the Enforcement Regulations of the Pharmaceutical Affairs Law.

Required Information

For each adverse event, the investigator and subinvestigator shall record the necessary information (onset date, disappearance date, severity, treatment, outcome, severity, treatment with the investigational drug, etc.) in the CRF. In addition, investigators and subinvestigators must determine the causal relationship between all adverse events and the investigational drug.

The following events will also be treated as adverse events

・Aggravation of primary or pre-existing disease

・Fluctuations in vital signs, electrocardiograms, physical findings, and laboratory values that the investigator and subinvestigators consider clinically problematic

If such abnormalities existed prior to inclusion in the clinical trial, they are considered the baseline condition of the subject.

All adverse events, including those that persist at the end of a clinical trial for an individual subject, should be followed to the extent possible until the subject recovers to the state prior to the adverse event, or until the event is fully investigated or no new information is available.

6.　Investigational plan

